### Secondary endpoints

Weight gain during pregnancy (weight measured at the end of pregnancy minus prepregnancy weight, as reported by the subject); systolic and diastolic blood pressure; pre-eclampsia diagnosis (systolic blood pressure ≥140 mmHg or diastolic blood pressure ≥90 mmHg occurring after 20 weeks of gestation and simultaneous proteinuria of ≥300 mg/24 hours); urinary tract infection; vaginal infections; intrauterus growth restriction (fetal ultrasound parameters) [18]; preterm birth (before 37th gestational week); Cesarean section; birth injury; macrosomia (birth weight above the 90th centile); maternal or neonatal intensive care admission.

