### Participant selection

Obstetrical staff will identify pregnant women recently diagnosed with GDM; following IMIP guidelines, a 75 g oral glucose tolerance test (OGTT) is routinely performed between the 24th and 28th gestational week. These patients will be approached by a member of the study team and permission will be sought after an explanation of the study goals. GDM women will be considered eligible for enrollment if they fulfill all the inclusion criteria and none of the exclusion criteria. Interested patients will be invited to sign a written informed consent.

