### Study design

This is an RCT to assess the effects of a 2-month water exercise program on GDM control and perinatal outcomes.

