### Pre-randomization evaluation

All diabetic pregnant women will have their clinical history recorded and will undergo a complete physical examination to identify diseases that do not allow for the use of the pool or for performing physical exercise.

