### Randomization

Randomization will be performed according to a computed-generated allocation (http://www.randomized.com). Pregnant women will be assigned, in a 1:1 ratio, to exercise intervention or usual care. Blinding of the study to the randomization arm is not possible due to the nature of intervention.

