### Aquatic exercise intervention

Participants commence the exercise session by performing stretching and an active warm-up of 5 minutes duration. Aquatic sessions include walking, walking backwards, swimming laps, jogging, step climbing and strength exercises in the water. After 35 minutes, the participants initiate a 5-minute cool down period.

Pool-based exercise classes will be completed in groups of four to six participants under the instruction of a physiotherapist. The exercise program will be conducted three times per week with each session lasting 45 minutes. This will be conducted from GDM diagnosis (26th to 28th gestational week) to the end of the third trimester (38th to 39th gestational week). Thus, an average of 30 training sessions will be planned for each pregnant woman.

The entire program will be developed in the thermal pool at IMIP; water temperature around 28°C.

All participants will use a heart rate monitor (Polar Electro OY) during the training sessions to ensure that heart rate is consistently under 70% of their age-predicted values.

A summary of the study design is presented in Figure 1.

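### Weight gain counted from self-reported prepregnancy weight includes gain before randomisation and recall error, so its comparison loses precision, without bias

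*Protocol article*

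**What the plan says.** The Protocol article, Secondary endpoints, defines weight gain during pregnancy as "weight measured at the end of pregnancy minus prepregnancy weight, as reported by the subject". The starting point is therefore a woman's own report of her weight before she conceived.

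The section Aquatic exercise intervention sets the treatment period: "This will be conducted from GDM diagnosis (26th to 28th gestational week) to the end of the third trimester (38th to 39th gestational week". Participant selection gives a slightly wider window for diagnosis: "a 75 g oral glucose tolerance test (OGTT) is routinely performed between the 24th and 28th gestational week". Under Randomization, "Pregnant women will be assigned, in a 1:1 ratio, to exercise intervention or usual care".

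The Analyses section compares continuous outcomes by an unpaired t test under intention to treat, and names no covariate. Before randomisation, women "will undergo a complete physical examination" to identify conditions that rule out the pool or exercise. The article does not say whether weight is recorded then.

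**The concern.** The outcome has three parts: gain between conception and randomisation, error in the reported prepregnancy weight, and gain after randomisation. Exercise can act only on the third. The first two still enter each woman's value and so enter the standard error of the t test.

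Weight gain is a secondary endpoint, and the trial of 72 women is sized on glucose. What is at stake is whether the weight result can be informative. A null finding could mean that exercise has little effect on weight, or only that the comparison was too noisy to show one. Part of that noise can be removed cheaply.

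**Working it through.** **Plan's own figure.** The article gives no SD, expected effect or power for weight gain, so there is nothing to reproduce. Its 30 per arm (Sample size, for glucose) serves only as a yardstick. At 80% power and two-sided 5% (sidedness assumed), 30 per arm detects a standardised difference of √(2/30) × (1.960 + 0.842) = 0.723.

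**Share of time before treatment.** From the stated weeks, 26/39 = 67% to 28/38 = 74%. If a woman entered at week 24, the earliest time for the diagnostic test, the lower figure would be 24/39 = 62%. These are shares of gestational time, not of kilograms or of variance.

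**Variance.** With independent parts,

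Var(total gain) = SD(before)² + SD(recall)² + SD(after)²,

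and the ratio to gain since randomisation is Var(total gain) / SD(after)². All SDs are assumptions: before 3–5 kg, recall 1–3 kg, after 2.5–3.5 kg. The ratio rises with the first two and falls with the third, so the extremes lie at the corners.

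| | Mildest | Most severe |
|---|---|---|
| Before, recall, after (kg) | 3, 1, 3.5 | 5, 3, 2.5 |
| Var(total gain) | 9 + 1 + 12.25 = 22.25 | 25 + 9 + 6.25 = 40.25 |
| Ratio | 22.25/12.25 = 1.8 | 40.25/6.25 = 6.4 |
| Share of variance from after randomisation | 55% | 16% |
| Standard error multiplied by | √1.816 = 1.35 | √6.44 = 2.54 |
| Detectable difference, total gain | 0.723 × 4.72 = 3.4 kg | 0.723 × 6.34 = 4.6 kg |
| Detectable difference, gain since randomisation | 0.723 × 3.5 = 2.5 kg | 0.723 × 2.5 = 1.8 kg |

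**Independence.** A correlation ρ between gain before and gain after adds 2ρ × SD(before) × SD(after). With ρ = ±0.3 (assumed) this is ±6.3 in the mildest case and ±7.5 in the most severe. The mildest ratio becomes 15.95/12.25 = 1.3 or 28.55/12.25 = 2.3. The most severe becomes 32.75/6.25 = 5.2 or 47.75/6.25 = 7.6.

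**Power under a second set of assumptions.** Three pairs of SDs for after and before (2 and 3, 2.5 and 4, 3 and 5 kg) were combined with recall error of 0, 2 or 3 kg and correlation 0 or 0.3, at 30 per arm. The variance ratio is 3.3 to 6.4. Power for a true 1.5 kg difference is 12–36% on total gain against 49–83% on gain since randomisation. For 3 kg it is 36–90% against 97–100%.

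**Bias.** Simulating 40,000 trials with a true effect of −1.5 kg, SDs of 2.5 (after), 4 (before) and 2 kg (recall), and 30 per arm gave mean estimates of −1.51 kg for total gain and −1.50 kg for gain since randomisation. The standard errors were 1.32 and 0.65 kg. They agree with the formula: √(2/30) × √(16 + 4 + 6.25) = 1.32 and √(2/30) × 2.5 = 0.65. The definition doubles the standard error here and leaves the estimate centred on the truth.

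**The case against.** The strongest reply is that nothing here is wrong. The endpoint is called weight gain during pregnancy and is defined as exactly that. Total gain is a clinical outcome in its own right, allocation is random, and covariate adjustment of a secondary endpoint is detail that a journal article can leave to a full protocol or SAP.

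Most of this stands. The article does not contradict itself, total gain is worth reporting, and an unseen analysis plan that adjusts for a measured entry weight would settle the point. But the article states both the definition and the test, so the point concerns a stated choice and not missing detail. Adjusting for entry weight also keeps the treatment question the same: earlier gain has the same expectation in both arms, so both analyses estimate the same effect, one with less noise.

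A reader might infer three stronger things, and the documents support none of them.

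- *That the noise swamps any effect of exercise.* With no SD, expected effect or recall error given, this cannot be shown. In the mildest case above, the randomised period carries 55% of the variance.
- *That chance imbalance in earlier gain creates spurious effects.* Imbalance does move the estimate in a single trial, but the t test's standard error already includes that variation. The false-positive rate stays at 5%.
- *That recall differs by arm because the trial is open* ("Blinding of the study to the randomization arm is not possible due to the nature of intervention"). This would require prepregnancy weight to be asked after allocation. The article does not say when it is asked, and clinical history is taken before randomisation.

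**Conclusion.** The point holds as one of precision. The weight-gain endpoint contains gain from before randomisation and recall error that exercise cannot alter, and the planned t test does nothing to remove them. Under the assumed independent SDs, the variance is about 1.8 to 6.4 times that of gain since randomisation, which multiplies the standard error by about 1.35 to 2.5. The direction is secure unless earlier and later gain are strongly negatively correlated. The size rests wholly on assumed SDs, because the article gives none.

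There is no bias as long as recall error is unrelated to arm, no rise in the false-positive rate, and no consequence for the glucose endpoint. This is a worthwhile improvement to a secondary endpoint.

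One related inconsistency affects how much gain is exposed to treatment. Study design states "This is an RCT to assess the effects of a 2-month water exercise program on GDM control and perinatal outcomes", whereas weeks 26–28 to weeks 38–39 span 38 − 28 = 10 to 39 − 26 = 13 weeks. These statements must be reconciled.

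**What to change.** Record measured weight at the pre-randomisation examination. Compare end-of-pregnancy weight between arms by ANCOVA with that entry weight as covariate and, if wanted, gestational age at randomisation. With entry weight in the model, analysing final weight or gain since randomisation gives the same treatment estimate. Keep total gain from reported prepregnancy weight as a descriptive figure by arm.

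Do not adjust for gestational age at the last weight. It is measured after randomisation and may be affected by treatment, since preterm birth is itself a secondary endpoint. Conditioning on it could bias a comparison that is now unbiased.

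The cost is a change of analysis wording if the examination already includes weighing, which the article does not state, and otherwise one weighing per woman. Trial status reports recruitment open since August 2013. Women already enrolled without an entry weight cannot be adjusted on a measured value, and their number should be reported. No extra women and no change to treatment are needed.

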### Pre-randomization evaluation

All diabetic pregnant women will have their clinical history recorded and will undergo a complete physical examination to identify diseases that do not allow for the use of the pool or for performing physical exercise.

### Randomization

Randomization will be performed according to a computed-generated allocation (http://www.randomized.com). Pregnant women will be assigned, in a 1:1 ratio, to exercise intervention or usual care. Blinding of the study to the randomization arm is not possible due to the nature of intervention.

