**Methods/Design:**

An RCT will be conducted at Instituto de Medicina Integral [name] (IMIP), Brazil. A total of 72 pregnant women will be studied; 36 gestational diabetics will undergo an aquatic physical exercise program in a thermal pool, 3 times per week over 2 months. The primary endpoint will be glucose level control and use of insulin; secondary endpoints will be the following maternal and fetal outcomes: weight gain during pregnancy, blood pressure, pre-eclampsia diagnosis, intrauterus growth restriction, preterm birth, Cesarean section, macrosomia and maternal or neonatal intensive care admission. Endpoints between intervention and control group will analyzed by t test for unpaired data and χ^2^ test, and the level of significance will set at <0.05.

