### Post-randomization evaluations

To ensure that similar guidelines for GDM clinical treatment are maintained for the two groups, IMIP obstetrical staff will undertake the ongoing GDM management of all trial participants for the period of the study. Participants are usually clinically evaluated at a minimum of every 2 weeks depending on GDM control, according to the IMIP guidelines for GDM. A capillary glucose test is performed at each clinical visit.

Self-monitoring of fingertip capillary blood glucose will be performed after overnight fasting, 2 h after breakfast, 2 h after lunch, and 2 h after dinner. The capillary glycemic profile will be determined every other week until 34 weeks of gestation, and weekly thereafter. All women will receive instructions to measure capillary glycemia with an Accu-Chek Advantage glucose meter (Roche Diagnostics, Indianapolis, IN, USA) and glucose blood strips. Insulin will be introduced when more than two glucose measurements are above the recommended value.

The mean capillary glucose profile will be analyzed post intervention (minimum of five determinations per woman). Insulin or oral hypoglycemia will be compared between the two groups.

All pregnant women will wear a pedometer (Yamax Digi Walker SW-200, Tokyo, Japan) during the whole study. Pedometer readings will provide a measure of physical activity to compare both groups.

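### Blinding is ruled out for the whole study on a reason that covers only the women and those who deliver or schedule the exercise; readers, outcome classifiers and the analyst could be masked cheaply

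*Protocol article*

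**What the plan says.** Under Randomization, the protocol article gives one sentence on masking: "Blinding of the study to the randomization arm is not possible due to the nature of intervention". It follows the statement of the allocation: "Pregnant women will be assigned, in a 1:1 ratio, to exercise intervention or usual care". No role is exempted.

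Other sections show who does what:

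- **Exercise** (Aquatic exercise intervention): "Pool-based exercise classes will be completed in groups of four to six participants under the instruction of a physiotherapist".
- **Diabetes care in both arms** (Post-randomization evaluations): "IMIP obstetrical staff will undertake the ongoing GDM management of all trial participants for the period of the study". The same section has the women measure their own capillary glucose and gives a numeric trigger for treatment: "Insulin will be introduced when more than two glucose measurements are above the recommended value".
- **Secondary endpoints**: the list includes "intrauterus growth restriction (fetal ultrasound parameters", together with birth injury, Cesarean section and maternal or neonatal intensive care admission.
- **Analyses**: unpaired t tests and chi-square tests by intention to treat. No masked analyst or coded arm is mentioned.

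The paragraph on methodological weaknesses in the Discussion does not mention open assessment.

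**The concern.** The reason given is narrower than the rule drawn from it. An exercise class cannot be hidden from the women who attend it, the person who teaches it or the person who books it. That says nothing about someone who measures a fetus on ultrasound, codes a newborn record or runs the tests.

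Two kinds of step are left open without need. The first is reading and classification: growth restriction comes from ultrasound parameters, and an outcome such as birth injury needs someone to decide whether a record qualifies. A borderline case can be placed according to expectation. The second is analysis: the Primary endpoint section offers several glucose summaries and names none as decisive, so an analyst who can see the arms can also see which summary favours exercise. A t test or chi-square test cannot separate either influence from an effect of exercise.

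**Working it through.** No figure in the plan belongs to this point, so the check is to set each role against the stated reason.

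| Role | Where it appears | Must know the arm because of pool exercise? |
|---|---|---|
| Women | Aquatic exercise intervention | Yes |
| Physiotherapist | Aquatic exercise intervention | Yes |
| Staff who allocate and schedule sessions | Implied by Randomization and by group classes | Yes |
| Obstetrical staff | Post-randomization evaluations | Not required, but they can learn it from the women |
| Ultrasound reader | Secondary endpoints (growth restriction) | No |
| Classifier of judged newborn and maternal outcomes | Secondary endpoints | No |
| Analyst | Analyses | No |

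The reason fully supports open status for the first three rows and does not support it for the last three. The obstetrical staff lie between: nothing in the intervention requires them to be told the arm, but masking them could only be partial.

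Next, which endpoints would gain if the last three rows were masked?

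1. **Growth restriction:** gains, because the reading itself would be made without the arm.
2. **Birth injury and similar judged items:** gain at the classification step.
3. **Endpoints resting on measured cut-offs** (pre-eclampsia by pressure and proteinuria, preterm birth by week, macrosomia by birth-weight centile): little to gain.
4. **Cesarean section, intensive care admission and insulin use:** little to gain, because the treating clinician's decision is the event, and a masked classifier would simply record it.
5. **Capillary glucose:** the readings gain nothing, because they are taken by women who know their arm. The analysis gains. The Primary endpoint section lists a mean capillary level (fasting and postprandial) and a number of readings above target. That is two types of summary over two meal states, or up to 2 × 2 = 4 comparisons if they are kept separate, with no ranking.

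The documents give no insulin rate, reading error or misclassification rate, so no size of bias can be computed from them.

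**The case against.** **Condensation.** A journal article commonly leaves masked analysts and coded data to the full protocol or analysis plan, and the sentence can be read as an ordinary open-label statement. Silence would indeed be no finding. Here, however, the article takes a position for the study as a whole and gives a reason that does not carry it. The objection limits the weight of the point but does not remove it.

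**Existing safeguards.** The same obstetrical staff manage both arms, expressly so that treatment guidelines stay alike, and insulin follows a numeric trigger. Both limit discretion. The trigger states neither a time window nor a total number of readings, so some discretion remains, but masking readers and analysts would not remove it.

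**A stronger reading that the documents do not support.** A reader might infer that open assessment endangers the primary insulin result and that masking would repair it. The abstract does say "The primary endpoint will be glucose level control and use of insulin", but the Primary endpoint section names only glucose measures. Insulin use is treatment given, not something read off a glucose log.

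One can assume 40% insulin use, no true effect, and a fall of 10, 15 or 20 percentage points in the exercise arm through biased prescribing. The exact rejection probability of the Pearson chi-square test at two-sided 5% is then:

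| Per arm | 40% v 40% | 40% v 30% | 40% v 25% | 40% v 20% |
|---|---|---|---|---|
| 36 (all enrolled) | 0.049 | 0.150 | 0.285 | 0.471 |
| 30 (after the planned dropout) | 0.049 | 0.123 | 0.230 | 0.392 |

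The arithmetic is sound, but the 40% and the shifts are assumptions with no basis in the documents. The table also describes prescribers who know the arm. A masked sonographer or analyst would pass a biased prescription through unchanged, so these figures are not the gain from the fix.

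**Who does the work.** The article does not say who performs the ultrasound, classifies outcomes or analyses the data. That masking needs no new staff is therefore an assumption.

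**Conclusion.** The point holds in a limited form. The Randomization section draws a study-wide rule from a reason that applies to the women, the exercise providers and the allocation or scheduling staff. Ultrasound reading of growth restriction, classification of judged outcomes, and an analysis with several unranked glucose summaries are left open although nothing in the intervention requires it.

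The size of any bias is unknown and cannot be derived from the documents. The benefit of masking falls mainly on a few secondary endpoints and on the analysis. It does not reach self-measured glucose, and it scarcely reaches decisions on insulin, Cesarean section or intensive care admission. The conclusion assumes that the readers, classifiers and analyst are not the same people who run or schedule the classes. Label: cheap improvement.

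**What to change.** Replace the blinding sentence with a statement by role:

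- Participants, exercise providers and allocation or scheduling staff cannot be masked.
- The existing sonographers, the staff who classify newborn and maternal outcomes, and the analyst work without the arm.
- The analysis data set labels the arms A and B until the analysis is final.
- Pool attendance is kept out of the clinic record, so that obstetrical staff are not routinely told the arm.

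Add a limitation to the Discussion: self-measured glucose and treatment decisions (insulin, Cesarean section, intensive care admission) remain largely open to knowledge of arm.

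**Cost:** a few sentences, a coded data set and a separate place for attendance sheets. No sample size, endpoint or clinical rule changes. **Downside:** masking will be partial because women may reveal their arm. If one person both schedules sessions and analyses the data, those tasks would have to be split.

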### Post-randomization evaluations

To ensure that similar guidelines for GDM clinical treatment are maintained for the two groups, IMIP obstetrical staff will undertake the ongoing GDM management of all trial participants for the period of the study. Participants are usually clinically evaluated at a minimum of every 2 weeks depending on GDM control, according to the IMIP guidelines for GDM. A capillary glucose test is performed at each clinical visit.

Self-monitoring of fingertip capillary blood glucose will be performed after overnight fasting, 2 h after breakfast, 2 h after lunch, and 2 h after dinner. The capillary glycemic profile will be determined every other week until 34 weeks of gestation, and weekly thereafter. All women will receive instructions to measure capillary glycemia with an Accu-Chek Advantage glucose meter (Roche Diagnostics, Indianapolis, IN, USA) and glucose blood strips. Insulin will be introduced when more than two glucose measurements are above the recommended value.

The mean capillary glucose profile will be analyzed post intervention (minimum of five determinations per woman). Insulin or oral hypoglycemia will be compared between the two groups.

All pregnant women will wear a pedometer (Yamax Digi Walker SW-200, Tokyo, Japan) during the whole study. Pedometer readings will provide a measure of physical activity to compare both groups.

